### Data handling

#### Participant numbering

Each participant will be allocated a unique four-digit identification number. Each participant will be identified in all study-related documentation by his/her study number and initials. A record of names linked to participants’ study numbers will be maintained by the research nurse and stored securely for administrative purposes.

#### Data capture and transfer

Data will be recorded on study-specific case report forms (CRFs) by the research nurse and directly into questionnaire booklets and diaries by participants. Photographs taken by research nurses will be saved, transferred and stored according to the Royal Devon and Exeter Hospital’s local policy. The images will be stored securely on the hospital system in accordance with data protection regulations.

#### Data entry

Completed paper CRF’s will be checked and signed by the research nurse before being sent to the clinical trials unit. Original paper CRF pages, questionnaire booklets and diaries will be posted to the trials unit at agreed time points for double-data entry onto a password-protected database in accordance with the trials unit standard operating procedures (SOP’s). Research nurses will also have the option of entering CRF data at agreed time points directly onto the study database via the study website. These data will not be double entered. Forms will be tracked using a Web-based study management system. Double-entered data will be compared for discrepancies using a stored procedure. Discrepant data will be verified using the original paper data sheets.

#### Data confidentiality

The research nurses will ensure that participants’ anonymity is maintained on all documents and images. Data will be collected and stored in accordance with the Data Protection Act, 1998. Within the trials unit, anonymised paper-based study data will be stored in locked filing cabinets within a locked office. Electronic records will be stored in a Structured Query Language (SQL) server database, stored on a restricted access, secure server maintained by Plymouth University. The website will be encrypted using Secure Sockets Layer data encryption (SSL). Direct access to the study data will be restricted to members of the study team, the Sponsor and the Peninsula Clinical Trials Unit. Access to the database will be overseen by the trials unit data manager and trial manager. Copies of study data retained at study sites (i.e. care homes) will be securely stored for the duration of the study prior to archiving.

#### Archiving

Following completion of study data analysis, the sponsor will be responsible for archiving the study data and essential documentation in a secure location for a minimum period of 5 years after the end of the study. No study-related records should be destroyed unless or until the sponsor gives authorisation to do so.

### Statistical methods

The study will be analysed using the statistical package SPSS v. 20 (IBM Corp, New York). Missing data will be investigated and the proportion missing will be recorded but are expected to be minimal. Multiple imputation methods or any specific imputation methods recommended by the authors of the questionnaire will be used to obtain realistic estimates of scores for future planning of questionnaire usefulness. All the questionnaires concerning acceptability of the socks will be scored and summarised using appropriate measures of central tendency and dispersion. Data on lacerations will also be summarised in a similar way. Agreement on wound grading between research nurses and a blinded tissue viability expert (AK) will be assessed from anonymised photographs using weighted kappa. Numbers of eligible residents, recruitment, attrition and loss to follow-up (as per the Consolidated Standards of Reporting Trials (CONSORT) diagram) will be reported as proportions, confidence intervals will be reported wherever appropriate. The main analysis will describe skin tear-free days and the incidence and severity of skin lacerations in each group.

The pilot study will determine the feasibility of how the outcomes can be measured. These will be used to inform the sample size of the full-scale randomised controlled trial. In that trial, we intend to compare the incidence of skin damage between the two groups on an intention-to-treat basis and the size of any wounds by objective assessors (research nurses). The clustering effects of homes will be an issue in the analysis of a future definitive randomised controlled trial, and sample size inflation will need to be considered for a mixed effects model with “homes” as a random effect.

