### Randomisation and blinding

Randomisation will be achieved by means of a Web-based system created by the Peninsula Clinical Trials Unit in conjunction with the study statistician. The participants will be allocated to the protective socks intervention or to standard care in equal proportions, using blocks of fixed size to generate the allocation sequence and achieve balance in the numbers of participants allocated to each group. Variable block sizes were considered but would provide no advantage since the number of participants recruited at each care home is likely to be small. Randomisation will be stratified by geographical area (i.e. Exeter, Exmouth/Sidmouth and Mid Devon).

The Web-based randomisation system created and maintained by the clinical trials unit will allow secure access via computers or other devices with Internet connectivity. Research nurses will be provided with log-in details and will perform randomisation from the care home by smart phone. The system ensures allocation is concealed prior to performing randomisation. Telephone randomisation will be available during working hours (09:00 to 17:00, Monday to Friday inclusive) in the unlikely event the Web-based service is unavailable.

Blinding will not be possible for participants or research nurses. Blinding is possible for the data analyst, however, by coding the group allocation in the data file.

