#### Procedure in the event of a skin tear injury

Care home staff or the community participant themselves will be asked to contact the research nurse by telephone immediately on becoming aware of an injury (i.e. as soon as possible on the day of the injury or the following morning in the case of an overnight injury). The research nurse will visit the resident or patient as soon as practicable (within 1 to 2 working days) of being contacted in order to collect the following:Date and approximate time of injury.Brief description of injury cause.Type of lower leg clothing and footwear worn at the time of injury (including whether protective socks were in place for participants in the intervention group).Size of injury (length, width and total area using a grid tracing method).Category of injury using the Payne-Martin and STAR classifications (as described in Appendix).A photograph of the injury.Information relating to the initial management of the injury (dressing type, referral to external healthcare professional such as GP, district nurse and hospital emergency department).

The research nurse will inspect the wound for signs of infection and will also check that the injury has been noted in the care home records (in the case of care home participants). Injured participants will complete outcome measure questionnaires 7 days post-injury.

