### Secondary outcomes

#### Skin tear assessments

There is no universally accepted classification system for the assessment of skin tears. Payne and Martin developed the first classification system in 1990, and this was updated in 1993 [1]. Problems associated with inter-rater reliability testing of the Payne and Martin classification system, and its poor utility in Australia, led to a study that resulted in the Skin Tear Audit Research (STAR) Classification System. The STAR Classification System is commonly used in Australia, with evidence of implementation reported within the UK [30].

In the main trial, skin lacerations will be measured in centimetres (length, breadth and area) and graded either according to Payne-Martin categories or the STAR Skin Tear Classification System. The photographs will inform an assessment of the reliability of the reported grading of the injury and will be performed by a tissue viability nurse specialist blinded to allocation.

Skin tear assessments will be performed upon learning of an injury, within 24 h if possible.

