## Appendix

### Skin tear categorisation

#### Payne-Martin classification

- Category I: Skin tear without loss of tissue. The epidermal flap either completely covers the dermis or covers the dermis to within 1 mm of the wound margin
  - o Sub category Ia: Linear type
  - o Sub category Ib: Flap type
- Category II: Skin tear with partial tissue loss
  - o Sub category IIa: Scant tissue loss (25% or less)
  - o Sub category IIb: Moderate to large loss of tissue (>25% loss of the epidermal flap)
- Category III: Skin tear with complete tissue loss.

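### The blinded photograph review is described for wound grade only, so it cannot show whether the unblinded nurses' call that an injury is a skin tear differs from a blinded call or differs by arm

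*Protocol article*

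**What the plan says.** All references are to the protocol article.

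- **Who is blinded.** Randomisation and blinding: "Blinding will not be possible for participants or research nurses". Only the data analyst can be.
- **How an injury enters the data.** "Care home staff or the community participant themselves will be asked to contact the research nurse by telephone immediately on becoming aware of an injury" (Procedure in the event of a skin tear injury). The nurse then visits and collects, among other items, "Category of injury using the Payne-Martin and STAR classifications" and "A photograph of the injury". Table 1 puts photographing, measuring and scoring of the wound in the column for a new injury.
- **What the blinded reader does.** Skin tear assessments: "The photographs will inform an assessment of the reliability of the reported grading of the injury", by a tissue viability nurse specialist who does not know the allocation. Statistical methods gives the same scope: "Agreement on wound grading between research nurses and a blinded tissue viability expert", using weighted kappa. No other blinded task is described.
- **The scales.** In the Appendix, Payne-Martin starts at "Category I: Skin tear without loss of tissue" and ends at complete tissue loss. Each of the five STAR categories is likewise worded as a kind of skin tear.
- **What depends on the call.** Outcome measures says the definitive trial's primary outcome will centre on tear-free days, incidence and severity. Ascertainment of injuries is among the pilot outcomes, and Trial objectives includes assessing how outcome data are captured. The main pilot analysis is a description by group.
- **Definitions.** A skin tear is defined in the Background and a healed injury under Primary outcome.

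**The concern.** Two judgements are made about each reported injury: whether it is a skin tear, and if so what grade it is. The first determines incidence and starts the count of days lost from tear-free days. The second bears only on severity. The blinded check is attached to the second.

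The first judgement is open to knowledge of allocation. Frail legs also acquire bruises, scrapes and chafing, and some of these will be hard to separate from a small tear. The list of expected device effects under Adverse and serious adverse events includes chafing, and tears caused by putting the socks on or taking them off. Only sock wearers can attract those labels, and the article does not say whether such tears also count as outcome events. Statistical methods then describes research nurses as objective assessors of wound size in the definitive trial, although the blinding section says that they cannot be blinded.

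At stake is what the pilot teaches. It could report good agreement on grade and leave unexamined the disagreement that matters more for the incidence outcome.

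**Working it through.** The article states no figure on this point, so there is none to reproduce. The check is first a reading of the text, then an illustration on assumed rates.

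**Step 1: what the weighted kappa can see.** Cross-classify each reported injury by nurse (tear, not a tear) and blinded reader (tear, not a tear). A weighted kappa on Payne-Martin or STAR needs a grade from both raters. All grades on both scales are tears, so the statistic uses only the cell where both say tear, or where the reader is obliged to supply a grade. The two disagreement cells have no place in it. However high the kappa, it carries no information on event status, overall or by arm.

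**Step 2: possible size for incidence.** All inputs are assumptions.

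Observed incidence = true incidence + (proportion with a borderline non-tear injury × probability that it is called a tear).

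Take true incidence 0.20 in both arms, so no sock effect, and borderline injuries in 0.10.

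| Called a tear, control v sock | Control | Sock | Risk ratio |
|---|---|---|---|
| 0.50 v 0.25 | 0.20 + 0.10 × 0.50 = 0.250 | 0.20 + 0.10 × 0.25 = 0.225 | 0.225 / 0.250 = 0.90 |
| 0.75 v 0.25 | 0.20 + 0.10 × 0.75 = 0.275 | 0.225 | 0.225 / 0.275 = 0.82 |

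Range over true incidence 0.10 to 0.30, borderline 0.05 to 0.15, control call rate 0.50 to 0.75 and sock call rate fixed at 0.25:

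- lowest: (0.10 + 0.15 × 0.25) / (0.10 + 0.15 × 0.75) = 0.1375 / 0.2125 = 0.65
- highest: (0.30 + 0.05 × 0.25) / (0.30 + 0.05 × 0.50) = 0.3125 / 0.3250 = 0.96

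Fixing the sock rate low makes the bias run one way. With the first row's call rates exchanged, the ratio is 0.250 / 0.225 = 1.11.

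**Step 3: against the pilot's precision.** With 45 per arm, the first row is a difference of 0.025 × 45 = 1.1 participants and the second 0.05 × 45 = 2.3. The 95% half-width for an incidence of 20% in one arm is 1.96 × √(0.20 × 0.80 / 45) = 0.117, about 12 percentage points.

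**Step 4: possible size for tear-free days.** Assume one counted injury per affected participant and 14 to 28 days to heal. The spurious difference in mean tear-free days is the incidence difference times the healing time: 0.025 × 14 = 0.35 days to 0.05 × 28 = 1.4 days, out of 112. At the widest difference in the range above, 0.15 × (0.75 − 0.25) = 0.075, it is 0.075 × 28 = 2.1 days. The exposure is mainly in incidence.

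**The case against.** The other side has real force, and three stronger readings should be set aside.

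- **A reader might infer that the nurse alone decides what counts, leaves no record of rejected injuries, and photographs only accepted tears.** The article says none of this. It names no sole decision-maker. The case report form is not shown and could hold a reject option. Table 1 ties the photograph to a new injury, although the heading of the procedure section speaks of skin tear injury, so the scope is ambiguous.
- **A reader might infer that the bias can be neither prevented nor measured.** That does not follow. Photographs are taken, a blinded specialist reads them, and a skin tear is defined. The material for a check exists; no such check is described.
- **A reader might infer that the pilot will make an ineffective sock look protective.** The pilot's analysis is descriptive and exists partly to examine how outcomes are captured. The risk ratios above rest on invented rates, and in the headline case the shift is about one participant per arm, well inside sampling error.

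It is also fair to say that a photograph is not clearly the better arbiter. STAR depends on whether wound edges can be realigned, which is easier to judge at the bedside. Photographs also cannot recover injuries that unblinded staff or participants never report.

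What stands is narrow but textual. The article states the scope of the blinded reading twice, and both times it is grade. This is therefore the stated use of the review, not merely detail left to a fuller document.

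**Conclusion.** The point holds in limited form. As described, the blinded review cannot reveal disagreement between nurse and blinded reader on whether an injury is a skin tear, nor whether that disagreement differs by arm. This follows from the text and the structure of the two scales and needs no numerical assumption.

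Its size is unknown. Under the assumed rates the spurious risk ratio runs from about 0.65 to 0.96 if nurses accept borderline injuries more readily in controls, and it exceeds 1 if they lean the other way. The effect on mean tear-free days is small, about 0.35 to 2.1 of 112 days. That outcome depends as well on the healing date, which the same unblinded nurse sets, with care home staff as necessary and no blinded check described.

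Because the pilot tests no effect, what suffers is its information on ascertainment and its incidence estimates for planning. This is a cheap improvement, not a flaw that undermines the pilot.

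**What to change.** 1. Confirm in the procedure section that every reported lower-leg skin injury is photographed, including any that the nurse does not regard as a tear. Table 1 suggests that this is already intended.
2. Add *not a skin tear* and *cannot tell* to the nurse's form and the blinded reader's form, both judged against the definition in the Background.
3. Report nurse-versus-blinded agreement on tear yes/no, by arm, before the weighted kappa on grade.
4. Describe incidence under both calls, as a sensitivity summary.

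The cost is one extra item on two forms and perhaps a few more photographs, read by a specialist who already reads them. The drawback is that some photographs will be inconclusive, hence the *cannot tell* row.

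The change will not recover unreported injuries and will not verify healing dates, and the report should say so. Which call should define an event in the definitive trial is best left open until the pilot has shown how often the two differ.

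### Wound severity is to be compared by unblinded nurses described as objective, and only among the injured, while the blinded photograph grade serves only as an agreement check

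*Protocol article*

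**What the plan says.** **Who measures.** In the protocol article, Statistical methods states an intention for the definitive trial. Incidence will be compared by intention to treat, and so will "the size of any wounds by objective assessors (research nurses", as a second item. Randomisation and blinding states: "Blinding will not be possible for participants or research nurses". The only blinding that section offers is at the analysis stage: "Blinding is possible for the data analyst, however, by coding the group allocation in the data file".

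**What happens at the injury visit.** Under Procedure in the event of a skin tear injury, the research nurse records the clothing worn, "including whether protective socks were in place for participants in the intervention group". The same nurse records "Size of injury (length, width and total area using a grid tracing method" and "Category of injury using the Payne-Martin and STAR classifications", and takes a photograph.

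**The blinded reading.** Skin tear assessments says the photographs inform a reliability check on the reported grade, "performed by a tissue viability nurse specialist blinded to allocation". Statistical methods gives the measure as weighted kappa. No other use of the blinded grade is stated.

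**The pilot itself.** "The main analysis will describe skin tear-free days and the incidence and severity of skin lacerations in each group".

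**The concern.** The nurses who assess wounds know the allocation. They also carry out the randomisation, hand out the socks and make roughly weekly contact. Calling them objective does not fit the article's own statement on blinding. Grid tracing and category assignment both involve judgement, and knowledge of the arm could move that judgement in either direction.

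The second issue is who is compared. A wound has a size or category only if a wound occurred, and wound occurrence is what the socks are meant to change. A comparison among the injured is therefore made in groups formed after randomisation.

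Severity is not a side issue. It is in the research question for the definitive trial, and Outcome measures names it alongside tear-free days and incidence as a focus of the future primary outcome. Trial objectives has the pilot evaluate two classifications as outcome measures and estimate outcome variability for sample size. If severity goes forward as an unblinded, injured-only measure, the definitive trial inherits both weaknesses.

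**Working it through.** No figure in the article tests this point, so the check is mainly textual, with one illustration.

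**Step 1: is allocation known when severity is judged?** Randomisation and blinding says the nurses are not blinded. The injury procedure has the same nurse note whether the socks were on, then trace and grade. So it is known. Coding the group for the data analyst does not help, because the measurement has already been made.

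**Step 2: does the agreement analysis protect the comparison?** Weighted kappa summarises overall agreement between nurse and specialist. It does not show whether disagreements run in one direction in one arm and the other way in the other arm. A respectable overall kappa is compatible with a difference by arm.

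**Step 3: what does the blinded reading cover?** It covers the category. Nothing in the article says that the photographs yield a blinded wound size. Size therefore stays nurse-measured whatever is done with the photographs.

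**Step 4: how large might the selection effect be?** Inputs:

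- 45 per arm and 112 days of follow-up (Method/design; Primary outcome).
- Background cites 14% of residents of one American nursing home with a skin tear per month. At a constant rate this gives 1 − 0.86^(112/30.4) = 0.426, or 0.426 × 45 ≈ 19 injured in an arm. That figure covers all body sites, so leg tears alone would be fewer.
- Assumed: 10% to 40% of controls injured; socks cut injuries by 25% to 50%; socks have no effect on severity at a given impact.
- Assumed model: impact is standard normal, a tear occurs above a threshold t, and severity has correlation ρ with impact.

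With a proportion p injured, mean impact among the injured is φ(t)/p. The difference in mean severity among the injured, socks minus control, is

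ρ × [φ(t_S)/p_S − φ(t_C)/p_C].

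| p control | p socks | φ/p socks − φ/p control | ρ = 0 | ρ = 0.3 | ρ = 0.6 |
|---|---|---|---|---|---|
| 0.10 | 0.075 | 1.887 − 1.755 = 0.132 | 0.00 | 0.04 | 0.08 |
| 0.40 | 0.20 | 1.400 − 0.966 = 0.434 | 0.00 | 0.13 | 0.26 |

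These two rows are the extremes over the assumed range. Units are SDs of severity across all impacts. A positive value makes the sock arm look worse although severity is unaffected.

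**Step 5: set this against the pilot's precision.** In the largest case, 0.40 × 45 = 18 controls and 0.20 × 45 = 9 sock wearers are injured. Taking a within-group SD of 1, the standard error of the difference is √(1/18 + 1/9) = 0.41 SD. In the pilot the bias would be hidden by sampling error. A larger trial shrinks the sampling error but not the bias.

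**The case against.** **The sentence concerns another trial.** The comparison is announced for the definitive trial; the pilot only describes severity. This stands. A reader might infer that a pilot result is biased, but the article plans no severity test or effect estimate in the pilot. What remains is that the descriptive summaries are meant to inform the next design.

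**Intention to treat is not claimed for size.** A reader might take the sentence as calling the wound-size comparison intention to treat. The phrase attaches to incidence, and size follows as a separate item. The point is that size among the injured is not a randomised comparison, not that the plan says otherwise.

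**The blinded grade cannot mend the size measurement.** This is correct: the blinded reading is of category. The article also does not say that every wound photograph is read, so a blinded grade for each wound cannot be assumed.

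**The selection effect rests on assumptions.** It is easy to construct a case in which the socks prevent mostly small tears, so that mean size per wound rises while total wound area falls. A reader might infer that the per-wound comparison will have the wrong sign. The article gives no data on which tears the socks prevent and fixes no per-wound mean, so that inference is not supported.

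**Other outcomes cover everyone.** Incidence and tear-free days include the uninjured and escape this selection. That limits the damage, although the date of healing is also identified by the visiting research nurse.

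**Measurement is what the pilot studies.** The agreement analysis is a reasonable check on nurse grading, and the choice of classification is left open. This argues against fixing the blinded grade as the outcome in advance. It does not argue against reporting that grade by arm.

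**Conclusion.** The point holds in a limited form. Describing the research nurses as objective assessors conflicts with the article's own statement that they cannot be blinded, and with an injury procedure in which the assessing nurse records sock use. The one blinded severity reading has no stated role beyond agreement. Size and category exist only for the injured, so a comparison by arm is not one of the randomised groups.

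The size of the bias is not known. Selection alone gives 0.00 to 0.26 SD against the socks under the assumed injury rates, sock effects and correlations, and zero if severity is unrelated to which tears the socks prevent. Assessor bias could add to this or offset it, and the article gives no basis for its size or direction. The consequence is for the severity estimates and outcome choice carried into the definitive trial, not for any test in the pilot.

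**What to change.** 1. In Statistical methods, replace the description of the nurses as objective with a statement that wound size is measured by unblinded research nurses.
2. Report the blinded photograph category by arm beside the nurse grade. Cross-tabulate nurse against specialist within each arm, as well as giving the overall weighted kappa. If photographs prove adequate, prefer the blinded category for between-arm severity, with the nurse grade as a flagged fallback.
3. Add a severity summary over all randomised participants: an ordinal scale with no tear as the lowest level and then the worst category, and total wound area with 0 for no tear, labelled as nurse-measured. State how participants withdrawn early are handled, so that they are not counted as tear-free by default. Label the injured-only figures as descriptive.

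**Cost.** A little more analysis, from tracings, categories and photographs already planned. Some photographs may be ungradable, and any wound photograph not already due for blinded reading would need one. Wound area remains unblinded after these changes.
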